### 7.5 CALCULATION OF THE GRACE RISK SCORE

The GRACE score will be calculated in accordance with current practice. The calculator is freely available electronically and may be downloaded as an app on most hospitals computers or smartphones. We will provide appropriate apps for smart phones and devices if needed. Since GRACE 1.0 inadequately captures all higher risk features it has been decided to include all patients with a GRACE 2.0 score of  $\geq 118$  but also to include those with a GRACE 2.0 score between 90 and 118 if they have other high risk features, such as significant ST-depression, anterior ECG changes, diabetes on treatment and if the initial Troponin rise if  $> 3 \times \text{ULN}$  for that hospital's criteria.

RAPID-NSTEMI[figure not shown]**7.6 RECRUITMENT**

Potentially eligible patients will be screened for enrolment as soon as possible at hospital admission, with all recruiting sites undertaking a screening process for all patients with chest pain admitted via A&E or Medical Admissions Units (MAU) or CDU. We would anticipate that the senior clinical nurse on the Unit would inform the team as soon as suitable patients arrive. A pageable research nurse/enrolling physician will review all patients with presenting symptoms as they present, assess any ECG changes, and order immediate Hs-Troponin, calculate the GRACE score once the result is available and if all inclusion criteria are met and there are no exclusion criteria, then the authorised person will gain ASSENT (English and Welsh sites) OR WRITTEN CONSENT, depending on local regulatory guidelines (Sites in Northern Ireland/Scotland may be required to obtain full written consent prior to randomisation). Eligibility can be confirmed by clinical staff who have appropriate training to assess recent onset cardiovascular symptoms indicative of acute coronary syndrome (this may be a physician or a specialist cardiac nurse/Advanced Nurse Practitioner). Posters will be displayed in all MAU, CCUs and cath labs, and we will arrange training days for the study. ASSENT will be in the form of a standard short information sheet that will be read out to the patient. The ASSENT process will be formally documented with date and time and signature of the person obtaining the assent. The Verbal Assent Information Sheet must be counter-signed by an independent witness, this should be a clinical staff member unrelated to the Rapid-NSTEMI trial. All site staff involved in the assent process will be required to sign the assent log provided by the LCTU. Once this has been obtained, the cath lab staff will be informed and the patient will be randomised.

**7.7 RANDOMISATION**

Randomisation will be performed by the research nurse/enrolling physician using a validated Interactive Voice Response (IVR) or Interactive Web Response (IWR) System ("Sealed Envelope Ltd") provided through the LCTU. Eligible participants will be randomly assigned in a 1:1 ratio to one of two arms:

- GROUP A: Immediate angiography with follow-on revascularisation if indicated  
or  
GROUP B: Standard angiography with follow on revascularisation if indicated, - within Guideline recommended times.  
Standard interim therapy such as LMWH/DAPT will be mandated in this group until angiography.

Randomisation will be stratified by hospital site, with minimisation within each hospital site strata for the Grace score category. Due to the nature of the intervention, blinding of the participants or the study team to the randomisation arm is not possible.

**7.8 INTERVENTION**

If randomised to immediate angiography (+/- intervention), the patient will be transferred to the cardiac catheterisation lab with no further avoidable delay similar to those on a STEMI pathway. At angiography the interventionist will decide, in accordance with usual criteria whether the patient should receive revascularisation (PCI or CABG) or whether they need no further management due to absence of flow limiting coronary obstruction, or whether the disease should be treated with medication alone. Routine practice including use of FFR to inform the clinician will be expected. All decisions will be documented in the eCRF. If the

RAPID-NSTEMI

[figure not shown]

appropriate intervention is PCI, then all things being equal the procedure will be completed at that sitting.  
Planned management of any non-infarct related artery (N-IRA) disease will be allowed and documented as being planned at the time of the first intervention.

If randomised to Group B the patient will be managed on an appropriate acute ward and receive subcutaneous LMWH, DAPT (Aspirin plus Ticagrelor/clopidogrel), and secondary prevention medication as per standard practice, including high dose statins. These patients will be listed for coronary angiography as per current standard care for N-STEMI patients for that hospital.  
Planned management of any N-IRA disease will be allowed and documented as being planned at the time of the first intervention.  
A screening log of potentially eligible but non-included patients with reasons, will be kept and reviewed regularly by the trial management group, screening log data will also be included in the reports to both the TSC and DSMC.

If the immediate Troponin is negative, patients will be considered to be suffering unstable angina and are NOT eligible for randomisation and will be managed according to the responsible physician standard of care for such patients. A second sample may be taken at 3 hours in line with current European guidelines, and if elevated, the participant may be randomised.

All patients will be approached as soon as possible following randomisation for formal consent to remain in the study: a patient information sheet and a consent form for signature will be given to the participant. Once written consent has been obtained participants allocated to group A will complete a quality of life baseline form (EQ-5D-5L).

A repeat Troponin will be undertaken within 24 hours after PCI.

An additional Troponin will be taken from the standard of care group prior to their planned angiography.

Table 1: Troponin & EQ5D-5L

|                                              | ADMISSION           | FOLLOWING RANDOMISATION | PRE ANGIO ?PROCEED | Within24 HOURS POST PCI     |
|----------------------------------------------|---------------------|-------------------------|--------------------|-----------------------------|
| GROUP A
EARLY ANGIO?PROCEED               | ASSENT*
TROPONIN | CONSENT                 |                    | TROPONIN
EQ-5D-5L
SAQ |
| GROUP B
STANDARD OF CARE
ANGIO?PROCEED | ASSENT*
TROPONIN | CONSENT                 | TROPONIN           | TROPONIN
EQ-5D-5L
SAQ |

\*or written consent, depending on local regulatory guidelines (applicable to sites in Northern Ireland/Scotland only).

RAPIDNSTEMI[figure not shown]

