| Biomarkers                  |              | •            |                         |                                             | •                             |               |                  |                                |                                |                                             |
| Echocardiogram                          |              |              |                         |                                             |                               | •             |                  |                                |                                | •                                           |
| EQ-5D-5L                                |              |              |                         |                                             | •                             |               |                  | •                              | •                              | •                                           |
| Seattle angina score                    |              |              |                         |                                             | •                             |               |                  | •                              | •                              | •                                           |
| Clinical Status: MACE events            |              |              |                         |                                             |                               | •             |                  | •                              | •                              | •                                           |
| Concurrent medication recording         |              | •            |                         | •                                           |                               | •             |                  | •                              | •                              | •                                           |
| Adverse Events (SAEs up to 12 month FU) |              | •            | •                       |                                             | •                             | •             | •                | •                              | •                              | •                                           |

Group A = 2 Troponins: on admission and within 24 hours post angiography  

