8.0 STATISTICAL ASPECTS

8.1 Power calculations

The power calculations are based on the results of several studies including the retrospective TIMACS study (11,22). Subsequently a post-hoc analysis using GRACE score was applied - patients with a GRACE risk score of >140 (equating to the third with the highest risk) in the early-intervention group had a primary outcome 13.9%, and in the delayed group of 21.0%, a reduction of 35% at 6 months. (HR=0.65; 95% CI, 0.48-0.89; P=0.006). We have decided to include admission for heart failure since there is clear evidence that this is an important outcome following admission with N-STEMI ACS (27) with rates between 5.6% (28) and 15% (29). The best data on new heart failure comes from Kaul (30) who reported a 12.8% incidence.

We have also calculated outcomes based on imputing data into the GRACE score 2.0 and on review of all data, concluded that a GRACE 2.0 score of ≥118 or ≥90 with further high risk clinical factors provides similar outcomes to the proposed event rates. Those with the intermediate GRACE 2.0 risk score (i.e. ≥90) are included providing they have one other high risk features not captured by GRACE 2.0 namely anterior “infarction”, ST segment depression, diabetes (on medication) and a Hs Troponin rise > 3x ULN.

Both the GRACE 2.0 of ≥118 or the GRACE 2.0 ≥90 with one of the risk factors, together with the heart failure data, will provide patient with an event rate ~19%.

Since outcomes have improved somewhat over recent times we have powered RAPID-NSTEMI conservatively to detect a 25% reduction in the composite primary end point.

Standard intervention arm (Group B), predicted primary outcome events = 19%.

Immediate Intervention arm (Group A) predicted primary outcome events = 14.25% (odds ratio of 0.71, relative risk reduction of 25%).

|                                       |        |
|---------------------------------------|--------|
| Effect size (relative risk reduction) | 25%    |
| MACE rate standard PCI group          | 19%    |
| MACE rate Immediate PCI group         | 14.25% |
| Number of patients per group          | 964    |
| Total number of patients in study     | 1928   |
| Total number including 5% drop out    | 2314   |
| 5% crossover and 8% CABG treatment.   |        |

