To achieve a power (1-β) of 80% with a (two sided) α=0.05, 964 patients are required in each arm. Assuming up to 5% drop-outs, 5% crossover, 8% needing CABG 1157 patients will be recruited to each of the treatment arms A and B, leading to a total of 2314 patients. (Risks to complete recruitment **APPENDIX VI**).

Based on the above, we consider the power calculations to be conservatively robust and the proposed sample size of sufficient power to detect a significant (and clinically important) reduction in primary endpoint. The calculations have been performed in STATA v14 using the  $\chi^2$  test of equal proportions with the support of the proposed trial statistician.

The trial will follow an adaptive design with closed DSMC review of standard of care event rates.

RAPID-NSTEMI[figure not shown]**8.2 STATISTICAL ANALYSIS PLAN**

Statistical analyses will be undertaken according to a pre-trial Statistical Analysis Plan (SAP) which will be prepared by the statistician employed on the study. Descriptive characteristics at baseline will be presented by treatment arm.

The Primary endpoint is composite outcome of major cardiovascular events (MACE–Death/MI/admission with heart failure) within 12 months, and secondary analyses will be performed for MACE at 30 days following identical methodology. All analyses will be performed following the intention-to-treat principle, with subsequent “immediate follow-on revascularisation” secondary analyses. The primary analysis will investigate the proportion of participants having a primary outcome in each arm, with OR and 95% confidence interval calculation. Additional analyses will compare events in Group A and B with a “time-to-event” endpoint of the primary outcome occurring up until 12 months. Two-sided 95% confidence intervals will be presented for the primary endpoint and all secondary end-point comparisons between groups. The detailed statistical analysis plan will be produced and agreed with the Trial Steering Committee, Sponsors and trial funders prior to trial initiation. The trial will be registered with [clinicaltrials.gov](https://clinicaltrials.gov).

A methods paper outlining the trial will be sent to an appropriate recognised journal for publication.

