### 10.10 CLINICAL EVENTS COMMITTEE (CEC)

A Clinical Events Review Committee (Chair [name]) will be established to determine whether a clinical event indicated by the site team is an appropriate clinical event. It will consist of a total of 3 experienced clinicians. Their reports will be used in the assessment of endpoints.

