**Myocardial infarction (MI):**

Myocardial infarction will require a hospital admission with one or more of the following:

Type 1: Spontaneous re-MI: Recurrent angina symptoms or new ECG changes occurring before PCI or <48 hours from PCI that is compatible with re-MI associated with an elevation of CK-MB, Hs-Troponin-I/T, or total CK beyond ULN and 20% or more above the previous value.

Type 4a: CK-MB or total CK >3 times the ULN within 48 hours following PCI. If the pre-PCI CK-MB or total CK level is higher than the ULN, there also needs to be:

Either the demonstration of a falling CK-MB or total CK level prior to the onset of the suspected event, or a subsequent peak of the cardiac biomarker of at least 20% above the previous value obtained prior to the onset of the suspected event.

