**Heart failure**

Heart failure will be defined as a hospital admission with any of the following symptoms and signs: worsening breathlessness, fatigue, fluid overload, pulmonary oedema, elevated venous pressure and elevated BNP. Confirmation of heart failure according to local expert judgement and evidence of impaired LV function will be required for the event to be classified as heart failure.

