**Image analysis**

All CMR images will be sent to the core laboratory at the National Institute for Health Research Biomedical Research Centre in Leicester for quality control and central analysis, with the interpreting clinicians blinded to patient information and allocated group.

Analysis will be qualitative and quantitative to include:

1. Image quality (assessed on a grade of 0 to 4 – unanalysable to excellent)
2. Presence of late gadolinium indicating infarction and location based on the AHA/ACC 17 segment model. This will be graded semi-quantitatively as previously described(2, 3) and quantified using the full-width half technique(4)
3. Presence and location of regional wall motion abnormalities and overall regional wall motion score(5)
4. Oedema when present will be quantified (for area at risk) on contrast enhanced cine short axis images(6-8) T1 mapping, thereby allowing quantification of myocardial salvage index
5. Microvascular obstruction from LGE and intramyocardial haemorrhage from quantification of T1 mapping(9)
6. Perfusion analysis at stress and rest scored based on the AHA/ACC 16 segment model(2, 3)
7. Quantitative analysis including end-diastolic volume, end-systolic volume, and ejection fraction

Quantification of global and regional longitudinal and circumferential strain using cine based tracking(10)

RAPID-NSTEMI

[figure not shown]

| Author   | Year | Journal           | No.            | Inclusion                                                                 | CMR timing                  | IS              | AAR    | MVO                    | Comments                                                       |
|----------|------|-------------------|----------------|---------------------------------------------------------------------------|-----------------------------|-----------------|--------|------------------------|----------------------------------------------------------------|
| Lemkes   | 2018 | EHJ               | 142 (124 CMR)  | Transient STEMI (acute STEMI with resolution of ECG changes and symptoms) | 4.3                         | 1.3% vs 1.5%    | N/A    | 2% vs 3%               | Timing of PCI does not have significant effect on infarct size |
| Layland  | 2017 | JAHA              | 73             | NSTEMI + 1 RF                                                             | 6.5±3.5d                    | 5.9±8.0%        | 16%    | 10 pts                 | T1m, T2m better than STIR                                      |

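### Scheduled MI testing differs by arm, and the Type 1 re-infarction rule does not exclude the index infarct's own marker rise, so the open-label primary composite can be biased in either direction

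*Protocol*

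**What the plan says.** The trial is open: protocol section 7.7 says that neither participants nor the study team can be masked. New MI is one of three components of the primary composite (7.2.1).

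Scheduled MI testing is not the same in the two arms. Section 7.8 states: "An additional Troponin will be taken from the standard of care group prior to their planned angiography". The footnote to Table 2 (7.9) reads "Group A = 2 Troponins: on admission and within 24 hours post angiography" and lists three for Group B. The pre-angiography column of Table 2 exists for the standard arm only, and both the ECG and the hs-troponin rows are ticked in it.

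Appendix II requires a hospital admission for any MI. Type 1 re-infarction, before PCI or within 48 hours of it, needs recurrent angina or new ECG changes compatible with re-infarction, together with a marker "beyond ULN and 20% or more above the previous value". For Type 4a, if CK-MB or total CK was already raised before PCI, the rule asks for either a falling level beforehand or a later peak at least 20% higher.

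Entry is early: the latest symptoms fall within 12 hours before admission and randomisation within 6 hours after it (7.3.1). A patient with a normal first troponin may enter on a raised 3-hour sample (7.4, 7.8).

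For heart failure, Appendix II says: "Confirmation of heart failure according to local expert judgement and evidence of impaired LV function will be required". Section 10.10 sets up a Clinical Events Committee (CEC) of three clinicians "to determine whether a clinical event indicated by the site team is an appropriate clinical event". Fuller definitions are deferred to the CEC Charter, the case report forms and the Manual of Operations.

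**The concern.** The Type 1 rule measures each marker against the one before it, whatever the direction of travel. Soon after the onset of an infarct the marker may still be climbing, so a 20% rise need not mean a second infarct. Whether such a rise is recorded depends on when samples and ECGs are taken, and that differs by arm. Any error of this kind enters the primary odds ratio, and a larger trial does not dilute it.

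The protocol is alert to the issue elsewhere. Section 6.3 criticises a previous timing trial for defining MI differently in its two groups. Section 6.0 notes that the benefit in the trial it rates best came from re-infarction in the delayed group before angiography. Here the written definition is common to both arms, but the opportunities to meet it are not.

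A lesser point concerns adjudication. Heart failure is first confirmed by local clinicians who know the allocation, and the protocol does not say that the CEC is masked. It does say so for the CMR core laboratory: "with the interpreting clinicians blinded to patient information and allocated group".

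**Working it through.** **Step 1. Where the rule can count the index infarct.** Let T0 be the admission marker and T1 the next one. The marker element is met when T1 exceeds the upper limit and T1 ≥ 1.2 × T0. Nothing is asked about the trend before T0. The early entry criteria make it plausible that T0 lies on the rising limb, and the CMR rationale in Appendix V itself assumes continuing necrosis until reperfusion.

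- Group B: the wait is long (audit median 60.8 hours for direct admissions, 7.4). A scheduled troponin and ECG fall at its end. Angina or an ECG change during the wait, plus the index rise, meets the rule.
- Group A: transfer is recommended within 90 minutes of randomisation (7.4), so there is little time before PCI. Its post-procedure troponin has only the admission value as a scheduled comparator. Symptoms or an ECG change within 48 hours of PCI, plus the index rise, meets the rule. In Group B the sheath sample removes that part of the rise from the post-procedure comparison.

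The schedule therefore creates opportunities for error in both arms, at different times. Type 4a rests on CK-MB or total CK, which Table 2 does not schedule, so the scheduled troponins bear on Type 1.

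**Step 2. Reproduce the design figure.** Inputs from 8.1: 19% in Group B, 14.25% in Group A. The protocol states: "To achieve a power (1-β) of 80% with a (two sided) α=0.05, 964 patients are required in each arm".

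n = [z(0.975)·√(2p̄(1−p̄)) + z(0.80)·√(p1(1−p1)+p2(1−p2))]² / (p1−p2)², with p̄ = 0.16625

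= [1.960 × 0.5265 + 0.8416 × 0.5254]² / 0.0475² = 963.2, rounded up to 964. The figure reproduces, and the sample size is not in dispute.

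**Step 3. Net spurious events in Group B, no true effect.** Take n = 1157 × 0.95 = 1099 per arm (recruited number less 5% drop-out). The number of spurious points is an assumption, because the protocol gives no misclassification rate. With difference d:

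chance of significance favouring Group A = Φ[(d − c)/s], where c = 1.960·√(2p̄(1−p̄)/n) and s = √([pA(1−pA)+pB(1−pB)]/n)

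For 14.25% against 15.25%: c = 0.02965, s = 0.01513, (0.01 − 0.02965)/0.01513 = −1.299, Φ = 0.097.

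| Net spurious points in B | Patients per 1099 | True rate 14.25% | True rate 19% |
|---|---|---|---|
| 0 | 0 | 2.5% | 2.5% |
| 0.5 | 5.5 | 5.2% | 4.8% |
| 1 | 11 | 9.7% | 8.6% |
| 2 | 22 | 25.6% | 21.5% |

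**Step 4. Net spurious events in Group A, planned effect true.** Group B at 19%, 964 per arm:

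| Net spurious points in A | Recorded rate in A | Apparent relative reduction | Power |
|---|---|---|---|
| 0 | 14.25% | 25.0% | 80.0% |
| 1 | 15.25% | 19.7% | 58.9% |
| 2 | 16.25% | 14.5% | 35.4% |

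**The case against.** Much can fairly be said for the plan.

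- The extra troponin cannot make an event alone. The rule also needs an admission and symptoms or ECG changes compatible with re-infarction. Section 7.10 repeats troponin for recurrent ischaemic symptoms in both arms, so the scheduled sample adds little for a patient who has angina while waiting. This stands. What remains is one additional ECG and troponin pair in Group B, and the missing trend condition in both arms.
- The asymmetry has a reason. A patient who has waited days needs a fresh pre-procedure value; one going to the laboratory soon after admission has a recent one. This stands, and it is why an extra Group A sample is not asked for.
- More MI before angiography in Group B may be a real cost of waiting, and it is a named secondary outcome (7.2.2). This stands. Striking out such events in one arm would create a new bias.
- The CEC reviews events, and its Charter may specify masking and tighter definitions. Those documents are not at hand. But masking alone would not cure the MI problem: a masked reader applying the Appendix II wording would still count the index rise.

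A reader might infer that the design favours immediate angiography. The documents do not support this, because Group A has its own route to spurious events after PCI. A reader might also infer that heart failure is ascertained on an arm-specific schedule, or settled locally. It is not: echocardiograms and follow-up contacts are the same in both arms, the event needs an admission and impaired LV function, and a CEC review follows. Nor is case-finding plainly deficient, since hospitalisations are reportable and any-cause admission is an outcome.

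**Conclusion.** The concern holds for MI. In an open trial, scheduled MI testing differs by arm, and the Type 1 rule lacks a stable-or-falling condition, which lets the index infarct's own rise count as a primary event. The documents fix neither the net direction nor the amount. The calculations show only how sensitive the result is: about 11 net misclassified patients per 1099 in Group B take the chance of a significant result favouring Group A from 2.5% to about 10% at a 14.25% base. About 10 per 964 in Group A (1% of 964 = 9.6) take power from 80% to 59%. These rest on assumed misclassification of 0.5 to 2 points and on the protocol's own event rates. All-cause death is unaffected.

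For heart failure the point is smaller: the first confirmation is local and unmasked, and CEC masking is not stated in the protocol, though the Charter may state it. No defensible figure can be put on this from the documents.

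**What to change.** 1. Amend the Type 1 wording in Appendix II, identically for both arms: a rise of 20% or more counts only from a marker shown to be stable or falling. Where that cannot be shown, adjudication requires new clinical evidence beyond the continuing index rise.
2. Keep the primary composite complete, without striking out Group B events. Pre-specify a sensitivity analysis that excludes MI identified only through scheduled samples or ECGs, including the Group B-only pre-angiography pair.
3. State in section 10.10 that the CEC adjudicates MI and heart failure masked to allocation, on packs redacted as far as possible. Local opinion nominates events; the CEC decides.

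The cost is wording in Appendix II, section 10.10 and the Charter, some redaction and adjudication work, and possibly slightly fewer counted MIs. No additional sampling is needed.
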